# Integrating nonpharmacologic strategies for pain with Inclusion, Respect, and Equity (INSPIRE): a digital health study protocol for a pragmatic multisite randomized controlled trial

**DOI:** 10.1186/s13063-025-09402-8

**Published:** 2026-01-08

**Keywords:** Chronic pain, Digital health, Health coaching, Health equity, Cognitive behavioral therapy, Mindfulness, Movement

## Abstract

**Background:**

Chronic pain (CP) is among the most common medical conditions, is the leading cause of disability, and is often refractory to medical treatment. The CDC and the American College of Physicians recommend nonopioid and nonpharmacologic treatment as first-line strategies, including cognitive-behavioral therapy (CBT), mindfulness-based interventions (MBI), and movement-focused interventions (MFI); however, only 3% of people with chronic pain (CP) have access to these evidence-based treatments. Patients from historically minoritized populations and those speaking languages other than English are particularly underserved and may go untreated. Stigma regarding CP and interventions to manage it present additional obstacles.

**Methods:**

The Integrating Nonpharmacologic Strategies for Pain with Inclusion, Respect, and Equity (INSPIRE) study evaluates a blend of these non-pharmacologic, evidence-based interventions using a pragmatic, parallel, two-arm RCT comparing intervention participants with wait-list controls. The INSPIRE intervention includes a 12-week curriculum delivered via a multilingual mobile app paired with weekly telehealth coaching. The primary outcome will be the “Pain, Enjoyment, and General Activity (PEG)” scores at 3 months. Secondary outcomes include PEG scores at 6 and 12 months, physical functioning, quality of life, sleep, depression, anxiety, and global satisfaction with treatment at 3, 6, and 12 months. Primary mediators to be examined include pain cognitions and health behaviors. Secondary mediators may include stigma and isolation, trust in healthcare providers, and both engagement and satisfaction with the INSPIRE intervention. The intention-to-treat primary analysis will be conducted with covariates including baseline measures of pain, anxiety, and physical function.

**Discussion:**

The full RCT protocol and intervention details are provided following the SPIRIT guidelines. Implications for improving treatment access via culturally and linguistically tailored digital health interventions are discussed along with the potential for health coaching to drive mobile app engagement.

**Trial registration:**

ClinicalTrials.gov ID NCT06183281. Trial registration data set can be found here: https://clinicaltrials.gov/study/NCT06183281 and in Additional file 1.

**Supplementary Information:**

The online version contains supplementary material available at 10.1186/s13063-025-09402-8.

## Background

### Unmet clinical need

Only 3% of people with chronic pain (CP) have access to evidence-based, non-pharmacologic, integrative treatments even though CP is among the most common and substantial diseases with an estimated incidence higher than that of diabetes, cancer, and heart disease combined [1–11]. CP substantially impacts physical and mental functioning, productivity, and quality of life; it is the leading cause of disability and is often refractory to medical treatment [3, 12, 13]. The CDC and the American College of Physicians recommend nonopioid and nonpharmacologic treatment for CP given the strong evidence for mind-body interventions such as cognitive-behavioral therapy (CBT), mindfulness-based interventions, and physical therapy (PT) and the recognition of harms caused by the inappropriate use of opioids for CP [12, 14–21].

### Health and healthcare disparities for pain

Health disparities populations (HDPs) (e.g., Black/African American (B/AA), Latinx) are more likely to have their pain underestimated by providers, are less likely to receive comprehensive diagnostic workups, are less likely to receive opioids, and receive less aggressive pain treatment [22, 23]. Patient-provider language concordance influences reported pain intensity and management plans for Latinx and Chinese patients [24]. Under-reporting of pain has been tied to cultural beliefs such as stoicism or desiring to be a good patient [25, 26]. Other patient-level factors include distrust in clinicians, internalized stigma, social isolation, and low expectations of treatment. Provider-level factors include implicit biases that manifest in poor decision making, failed treatment coordination, and poor communication. Health-system factors include less access to services and less availability of treatments like CBT or PT, particularly for HDPs [27–29].

Stigma is a fundamental cause of health disparities [30, 31]. Stigma contributes to disparities by creating obstacles to socioeconomic resources (e.g., education) and by initiating a cascade of psychological, behavioral, and biological responses that undermine health and contribute to social isolation [30, 32]. Low-income minorities who experience stigma based on race, poverty, or medical diagnoses (e.g., psych, substance use disorders (SUD)) will have greater difficulty accessing and accepting CP treatments unless the stigma(s) is also addressed.

#### The need for scalable innovations to improve access

CBT is considered the gold standard for CP management across diverse populations, although most patients in need do not receive it [18, 27, 28, 33–35]. Acceptance and mindfulness-based interventions (MBI) have also received broad support, but access has been even more limited [27, 28, 36–43]. Newer “third wave” psychotherapies such as Acceptance and Commitment Therapy and mindfulness-based cognitive therapy have blended traditional CBT with MBI, creating important new tools in need of innovative plans to improve access [27].

Movement-focused interventions (MFI) include stretching, strengthening, and mobility exercises to improve function, physical conditioning, disability, and health. Despite MFI being considered part of gold-standard treatment for most CP conditions, patient motivation and adherence are highly problematic [44–48]. MFI has also been successful blended with CBT, MBI, and third wave psychotherapies, but further investigation is needed [49, 50]. Additionally, a recent comprehensive review of the chronic pain management literature identified the pressing need for more pragmatic RCT’s, innovative implementation strategies, cultural/linguistic adaptations, and the exploration of digital tools that extend reach and reduce cost [27, 28].

#### Imagining a HDP-inclusive digital solution

Digital health has received support as a means of assessing and monitoring patients, optimizing integrative interventions, and improving CP outcomes [51–55]. Both internet and app-delivered interventions have demonstrated efficacy for depression, anxiety, and pain but have rarely been culturally or linguistically adapted [56–62]. Digital pain assessments may lower stigma and improve accuracy while digital CBT and MBI substantially increase reach, reduce cost, and remove other barriers to treatment [56, 57, 63–65]. Virtual MFI has strong potential to increase rehabilitation access and has been shown to be as effective as in-person MFI [66–69]. As with most digital interventions, sustaining patient engagement can be challenging. Preliminary studies have shown that hybrid models that blend coaching with digital CBT/MBI/MFI can improve engagement while maintaining positive outcomes even when the clinician contact is modest [70–76].

Based on prior experiences, both providers and patients may assume that digital health interventions will be unable to address the social isolation and need for social support often found in CP patients with complex social histories. Fortunately, the inclusion of a personal telehealth coach and structural features such as digital discussion forums, live (online) meditation groups, zoom support groups, personal text messages (even when automated), and linkages with the primary care team can still produce a sense of connection and rapport while maintaining the efficiency, lower cost, and greatly improved access to evidence-based care [77, 78].

Most current CP apps have not been validated, are not integrative, and have not taken cultural, linguistic, or digital literacy needs into account. Moreover, sustaining engagement and reducing social isolation with a mobile app has proven difficult without the concurrent support of a health care provider or social network. More efficient and scalable solutions with linguistic and cultural adaptations are needed to serve a diverse population with CP. The INSPIRE intervention has the potential to be a cost-effective alternative to the current standard of care which leaves many patients with suboptimal pain control.

#### Objective

We developed a culturally tailored, trilingual mobile phone app that blends CBT, MBI, and MFI delivered over 12 weekly modules and supported by weekly health coaching to address non-malignant chronic pain in adult primary care patients. This Phase III clinical trial will assess the effectiveness of this intervention and examine potential mediators. We hypothesize that INSPIRE participants will show significantly greater reductions in PEG scores (i.e., pain intensity, interference of enjoyment, and reductions in general activities) from baseline to 3 months (i.e., primary outcome) in comparison to waitlist controls with additional assessments at 6 and 12 months. Secondary outcomes will include the HEAL CDE measures and analysis of potential primary mediators (e.g., catastrophizing, self-efficacy, psychological flexibility) and secondary mediators (e.g., trust, lower stigma).

## Methods

### Trial design

The efficacy of the INSPIRE intervention will be determined by a multisite, parallel, two-arm pragmatic RCT comparing intervention participants with waitlist controls over a study period of 12 months. The primary outcome will be PEG scores at 3 months with secondary outcomes including PEG at 6 and 12 months, and physical functioning/quality of life, sleep, depression, anxiety, and global satisfaction with treatment at 3, 6, and 12 months. Secondary analyses will also determine if primary mediators of pain cognitions (catastrophizing, psychological flexibility, pain self-efficacy) and health behavior (behavioral activation, exercise, movement) and secondary mediators of stigma and isolation, trust in healthcare, and satisfaction with the INSPIRE intervention play a role in improved pain outcomes.

The feasibility and acceptance (F&A) of this research protocol was first assessed in a 3-month, single-arm pilot of *n*=24 participants (8 from each language group). F&A outcomes included the success of participant recruitment and retention, patient adherence, intervention fidelity, data collection tools and schedule, and participant satisfaction. Feedback on the trial methodology and the mobile app was collected and used for optimization prior to the start of the RCT. The study protocol is summarized in the flowchart (Fig. 1). The Study protocol adheres to the Standard Protocol Items: Recommendations for Interventional Trials (SPIRIT) 2025 guidelines [79]. The SPIRIT Checklist can be found in Additional file 2, and the “SPIRIT Figure” study timeline can be found in Table 1.

**Fig. 1 Fig1:**
[figure not shown]
Flowchart of the INSPIRE study

**Table 1 Tab1:** “SPIRIT figure” study timeline

	Trial Period						
	Enrollment		Post-randomization				
**Timepoint**	Screening	Baseline	3mo	5mo	6mo	11mo	12mo
**ENROLLMENT**							
Eligibility Screen	X						
Informed consent	X						
Randomization		X					
**INTERVENTION or comparator**							
INSPIRE Intervention		X	X	X		X	
Waitlist Control		X					
**ASSESSMENTS**							
Primary Outcome							
PEG [80]		X	X		X		X
Secondary outcomes							
Quality of life (WHOQOL)		X					X
PROMIS Physical functioning 6b [81]		X	X		X		X
PROMIS Sleep Disturbance 6a [82]		X	X		X		X
Sleep duration [83]		X	X		X		X
PHQ-8 (Depression) [84]		X	X		X		X
GAD-7 (Anxiety) [85]		X	X		X		X
Global Impression of Change [86]			X				X
TAPS-1 & TAPS-2 (Substance Use) [87]		X	X		X		X
Primary Mediators							
Pain Catastrophizing [88]		X	X		X		X
Psychological Inflexibility [89]		X	X		X		X
Pain Self-Efficacy [90]		X	X		X		X
Behavioral/Social activation [91]		X	X		X		X
Secondary Mediators							
PROMIS Social isolation 8a [92]		X					X
Internalized Stigma [93]		X					X
Healthcare Relationship Trust [94]		X					X
Adherence/Engagement			X				X
Mobile App Rating Scale [95]			X				
Other Covariates							
Demographics		X					
Digital Health Literacy [96]		X					

### 2.2 Study setting

This multisite study recruits from adult primary care clinics that represent two distinct health care systems located in a diverse, urban setting, the San Francisco Bay Area. These systems include a large academic health center (UCSF Health) and a network of community safety net clinics for the urban underserved (San Francisco Health Network; SFHN) managed by the San Francisco Department of Public Health (SFDPH). At UCSF Health, patients are majority non-White: 47% White, 24% Asian, 10% Latino, 9% African-American, and 10% other ethnicities. The payor mix is diverse, with 53% private insurance, 30% Medicare, 13% Medi-Cal, and 4% self-pay. SFHN serves 125,000 diverse patients and is comprised of 10 community safety net hospitals, including clinics which serve majority Chinese, Latinx, and Black/African American patients. At SFHN, patients served in the outpatient setting are majority non-White: 13% White, 23% Asian, 43% Hispanic/Latinx, and 13% Black/African American, and a majority have public insurance: 60% Medi-Cal, 23% Medicare, 3% private, and 5% uninsured. The INSPIRE intervention is delivered via mobile app or web browser using existing patient devices. The health coaching element is entirely remote, taking place over scheduled Zoom video visits. In the event of wifi or other technical difficulties, coaching will be delivered by telephone.

### Participants

#### Participant eligibility

Participants must be (1) age 18 or older; (2) speak English, Spanish, or Cantonese; (3) have a UCSF Health or SFHN PCP; (4) be willing to use a smartphone (iOS or Android – either their own or one provided by the study); (5) have chronic, non-malignant pain for at least 3 months; and (6) be willing to participate in a 12-month patient-centered CP management study where they will be randomized into one of two comparison arms. Spanish and Cantonese languages were chosen in addition to English due to their high prevalence in the San Francisco Bay Area. Any individuals with conditions that prevent informed consent (e.g., dementia, active psychosis) and patients with chronic pain-related surgery scheduled in the next 12 months will be excluded. Patients will not be excluded if they have a current SUD, mood disorder, or anxiety disorder. Participants are allowed to participate in other concomitant pain management interventions, including procedural interventions (e.g., joint injections), during the 12-month study but are asked to report these treatments. Pharmacotherapy interventions (e.g., opioids) are not assessed due to patient concerns voiced during the intervention development phase regarding potential unwanted changes to their medication regimen that could result from study participation.

##### Recruitment: Participant identification, screening, and consent

Study clinical research coordinators (CRCs) will utilize a HIPAA partial waiver of consent to identify potentially eligible patients using ICD-10-CM codes in the electronic health record [97, 98]. ICD-10 codes include those commonly used for chronic pain as well as more specific codes that often indicate conditions that cause chronic pain (e.g., low back pain, osteoarthritis, spinal stenosis, etc.). PCPs will be sent lists of their identified patients and asked to indicate those that should not be contacted for study recruitment. The remaining potentially eligible patients will be screened for eligibility by telephone by culturally and linguistically concordant staff. Those who consent to participate will complete baseline measures and be randomized. Participants may receive up to $270 for participation over the 12-month study period based on completion of each timepoint assessment.

#### Participant randomization

We will randomize at the level of the patient. While this poses a modest risk of provider contamination between intervention and control participants, providers will not receive any communication from the study team after enrollment. We have further addressed the potential effect of contamination by increasing sample size, allowing detection of smaller intervention effects.

Participants will be stratified by 4 demographic groups (Cantonese-speaking, Spanish-speaking, Black/African American English-speaking, and multi-cultural English-speaking) and randomly assigned 1:1 to either the INSPIRE intervention (Group 1) or control groups (Group 2). The CRC will utilize random block randomization to maximize balance between treatment groups throughout accrual while ensuring the randomization sequence remains unpredictable. A random allocation sequence was generated using a computer, where treatment groups were labeled as Group 1 or 2. After participants consent to study participation and complete baseline measures, clinical research coordinators will assign the next available study ID number in sequence, identify the allocated group, and inform participants of their assignment. The study ID number and Personal Health Information (PHI) will be stored in a HIPAA-compliant manner (REDCap) along with the intervention assignment (Group 1 or 2). Study personnel responsible for outcome evaluations will be blinded to which Group 1 or 2 represents.

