### Sample size justification

The sample size calculation was based on the primary analysis comparing the primary outcome (PEG scores) between the INSPIRE and control groups at 3 months. Based on the literature, we expect to observe an effect size of 0.3 in PEG score at 3 months [57, 58, 60, 70, 119, 120]. With a power of 0.8 and Type I error of 0.05 in a two-sided independent t-test, assuming 73% retention, a sample size of 586 (293/group) is needed at the enrollment to identify such an effect size at 3 months.

Although we will use Holm’s step-down procedure to adjust for multiple comparisons in secondary analyses, we will take a conservative approach in the power calculation for secondary analyses using Bonferroni with an individual Type I error of 0.01 to control for the family-wise Type I error in 5 comparisons on secondary outcomes. The sample size of 586 (293/group) at the enrollment will provide a power of 0.8 to detect an effect size of 0.366 (a group difference of 0.366*SD) in secondary outcomes between the INSPIRE and control groups. We consider the detectable effect sizes realistic that we expect to observe in the study. With a less conservative Holm’s step-down approach than Bonferroni that we will use in actual secondary analyses to adjust for multiple comparisons, the planned sample size will detect a smaller effect size than 0.366 with a power of 0.80 for secondary outcomes. Adverse events, severe adverse events, and unanticipated problems during the study will be summarized with frequencies and percentages and compared between the treatment groups using Fisher’s exact test or Chi-squared test as appropriate.

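### The claimed sample-size increase against contamination cannot be found in the sample-size calculation, whose own figures (586, 73% retention, 0.366) do not agree with one another

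*Protocol article*

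**What the plan says.** Under Participant randomization, the protocol article chooses to randomise individual patients, 1:1. It concedes a drawback: "While this poses a modest risk of provider contamination between intervention and control participants". Two mitigations follow. Providers hear nothing from the study team after enrolment, and the sample size was raised: "We have further addressed the potential effect of contamination by increasing sample size, allowing detection of smaller intervention effects". No contamination rate, diluted effect or inflation factor is given.

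Under Sample size justification, the primary calculation starts from "Based on the literature, we expect to observe an effect size of 0.3 in PEG score at 3 months". The test is set out as "With a power of 0.8 and Type I error of 0.05 in a two-sided independent t-test". The result is worded: "assuming 73% retention, a sample size of 586 (293/group) is needed at the enrollment" to identify an effect of that size. Retention is the only allowance named.

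The same section then takes the secondary outcomes at an individual Type I error of 0.01 and says that the 586 enrolled "will provide a power of 0.8 to detect an effect size of 0.366".

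**The concern.** The two sections describe the same 586 patients differently. One says the number was raised so that effects smaller than expected can be detected. The other says the number is what the expected effect itself requires. If all 586 are needed for 0.3, nothing is left over for a smaller effect. If part of the 586 is a margin, it is wrong to call 586 the number needed for 0.3.

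This matters because contamination moves the between-arm difference towards zero, and the claimed increase is part of the argument for randomising individuals. A reader of a null 3-month PEG result should be able to tell how much dilution the design could absorb. The article gives no way to tell, and its other figures point in two directions.

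**Working it through.** **Inputs.** From Sample size justification: effect 0.3 SD, power 0.80, two-sided alpha 0.05, independent t-test, 73% retention, 586 enrolled (293 per arm); for secondary outcomes, alpha 0.01 and detectable effect 0.366. From Participant randomization: allocation 1:1. The dilution of the effect is not stated anywhere. I assume 5% to 20% and model it as d = 0.3 × (1 − c), where c is the share of the effect lost.

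**Step 1: reproduce 586.** The normal approximation is n per arm = 2(z₀.₉₇₅ + z₀.₈₀)²/d² = 2(1.960 + 0.842)²/0.09 ≈ 174.4, so 175. The t-test gives 175.4, so 176. Enrolment at 73% retention is 176/0.73 = 241.1 per arm. That is 482 in total before rounding each arm up, or 2 × 242 = 484 after. The stated 586 is 586 − 484 = 102 higher (102/484 = 21%), so it is not reproduced.

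Other conventions do not reproduce it either: a one-sided test gives 382, and multiplying by 1.27 instead of dividing by 0.73 gives 448. Changing one stated input comes close in three ways:
- 60% retention: 176/0.60 = 293.3 per arm, about 586 in total
- alpha 0.025: 584
- power 0.87: 584

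**Step 2: use 0.366 as a cross-check.** At alpha 0.01 and 80% power, 0.366 needs 176.0 per arm by t-test, and 176/293 = 60.1%. With 73% retained, 293 × 0.73 = 213.9 per arm, the detectable effect would be 0.332. So both outputs in that section, 586 for 0.3 and 0.366 for the secondary outcomes, rest on about 176 analysed per arm. That means either 60% retention or an unstated factor of 213.9/176 = 1.215 on top of 73%.

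**Step 3: power for the 3-month PEG contrast under dilution** (two-sided t-test, alpha 0.05).

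| Dilution c | Effect | About 176 per arm | About 214 per arm |
|---|---|---|---|
| 0% | 0.300 | 80% | 87% |
| 5% | 0.285 | 76% | 84% |
| 10% | 0.270 | 71% | 80% |
| 15% | 0.255 | 66% | 75% |
| 20% | 0.240 | 61% | 70% |

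The effect detectable with 80% power is 0.299 at 176 per arm, which leaves no margin. At 213.9 per arm it is 0.2715, so the dilution that can be absorbed is 1 − 0.2715/0.3 = 9.5%. At exactly 10% dilution, power is 79.6%, shown as 80%.

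**The case against.** The strongest reply is that the margin exists and is merely unexplained. On the stated inputs about 484 would do, 586 are enrolled, and at 73% retention the trial can detect 0.27. That is a larger sample able to detect a smaller effect, as Participant randomization claims. This stands to a point: a reader might infer that the design has no margin and that any contamination takes power below 80%, but on the stated 73% retention that is wrong, since power is still 84% at 5% dilution. However, the article does not call the surplus a contamination allowance. The 0.366 figure also fits only if the surplus has already been used by lower retention or another inflation.

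It can also be said that the increase may be relative to some smaller target not shown, and that a condensed article need not print every factor. That would excuse a missing detail. It does not excuse calling 586 the number needed for 0.3, nor printing figures that disagree.

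Finally, the practical effect may be small. The contamination described runs through providers, who receive no study communication, while app and coaching go straight to participants. The planned mixed model may also do better than an unadjusted t-test. If the baseline correlation were 0.5 (an assumption), 176 per arm would give about 83% power at 10% dilution: 0.27/√(1 − 0.25) = 0.312, ignoring clustering. Both points lower the urgency. Neither supplies the allowance that the text says was made.

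**Conclusion.** The concern holds in a limited form. The claimed increase for contamination cannot be traced to the stated calculation, and 586, 73% retention and 0.366 cannot all be right under that calculation.

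The size depends on which analysed number is true, and the article does not settle this. With about 176 per arm there is no contamination margin. With about 214 per arm there is one, but only up to about 9.5% dilution.

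Two firmer readings are not supported. The documents do not show that power drops below 80% as soon as any control is contaminated; that follows only on the 176-per-arm reading. Nor do they show that the surplus of about 100 patients is the contamination margin; nothing says so, and 0.366 speaks against it.

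The power figures rest on an assumed dilution range and an unadjusted t-test. They ignore any gain from baseline and repeated measures and any loss from clustering.

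**What to change.** First, state under Sample size justification the retention and any inflation factor actually used, and make 586, 73% and 0.366 agree. Then take the option that matches:

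- **If about 176 per arm is the true analysed number:** delete the contamination sentence under Participant randomization and say that 586 is sized for an undiluted effect of 0.3. A line giving power under assumed dilution (about 71% at 10%, 61% at 20%) would help readers.
- **If 73% retention holds:** restate the primary power as 87% at 0.3, with a detectable effect of about 0.27, and the secondary detectable effect as about 0.33. Limit the contamination claim to about 9% dilution.

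In either case, a null primary result should not be described as protected against contamination beyond that limit.

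The cost is wording in two sections and a line of power figures, with no added patients. The drawback for the authors is that the stated protection against contamination becomes less favourable.
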